## Abstract

**Background:**

Aphasia affects the ability to speak, comprehend spoken language, read and write. One third of stroke survivors experience aphasia. Evidence suggests that aphasia can continue to improve after the first few months with intensive speech and language therapy, which is frequently beyond what resources allow. The development of computer software for language practice provides an opportunity for self-managed therapy. This pragmatic randomised controlled trial will investigate the clinical and cost effectiveness of a computerised approach to long-term aphasia therapy post stroke.

**Methods/Design:**

A total of 285 adults with aphasia at least four months post stroke will be randomly allocated to either usual care, computerised intervention in addition to usual care or attention and activity control in addition to usual care. Those in the intervention group will receive six months of self-managed word finding practice on their home computer with monthly face-to-face support from a volunteer/assistant. Those in the attention control group will receive puzzle activities, supplemented by monthly telephone calls.

Study delivery will be coordinated by 20 speech and language therapy departments across the United Kingdom. Outcome measures will be made at baseline, six, nine and 12 months after randomisation by blinded speech and language therapist assessors. Primary outcomes are the change in number of words (of personal relevance) named correctly at six months and improvement in functional conversation. Primary outcomes will be analysed using a Hochberg testing procedure. Significance will be declared if differences in both word retrieval and functional conversation at six months are significant at the 5% level, or if either comparison is significant at 2.5%. A cost utility analysis will be undertaken from the NHS and personal social service perspective. Differences between costs and quality-adjusted life years in the three groups will be described and the incremental cost effectiveness ratio will be calculated. Treatment fidelity will be monitored.

**Discussion:**

This is the first fully powered trial of the clinical and cost effectiveness of computerised aphasia therapy. Specific challenges in designing the protocol are considered.

**Trial registration:**

Registered with Current Controlled Trials ISRCTN68798818 on 18 February 2014.

## Background

Stroke is the largest cause of disability in the United Kingdom with communication impairment affecting one third of survivors [1]. Aphasia is the most common communication impairment acquired post stroke. It is a disorder of language which may affect understanding, expression, reading and writing. Speech and language therapy (SLT) is often received regularly initially but rarely continues after the first few months. Medical instability, fatigue and confusion may reduce full engagement with language therapy in the early weeks post stroke, reducing the opportunity for people to participate in treatment. There is evidence that people can continue to improve their language skills for several years [2]. As the consequences of aphasia remain a problem long term, investigation of interventions to reduce this health burden in the chronic stages post stroke is crucial. The National Stroke Strategy [1] recommends people receive rehabilitation for as long as they benefit from it. Treatment of aphasia that persists beyond the first few months post stroke is often not available through NHS services in the United Kingdom as ongoing therapy is costly through face-to-face SLT and places greater demands on limited resources.

Meta-analysis in a Cochrane review [2] of SLT for aphasia following stroke suggests some effectiveness of aphasia therapy [2]. Adequately powered randomized controlled trials (RCTs) in this field are rare except for recent studies of SLT intervention in the first few weeks post stroke. Laska *et al*. [3] randomised 123 patients with aphasia to receive 45 minutes of SLT a day for 21 days, starting within two days of stroke onset, or no SLT intervention. Severity of the aphasia was not reduced. A recently completed study, ACT NoW [4], randomised 170 people in hospital post stroke to SLT intervention or attention control (informal conversation with paid visitors) for up to four months. No significant differences between groups were shown and the authors suggested that the intervention may have been provided too early in the stroke pathway. As aphasia persists for many stroke survivors, therapy in the longer term also warrants investigation using adequately powered RCTs. Although rapid spontaneous recovery may occur in the first few months, there is preliminary evidence to suggest targeted and intensive SLT treatments can promote further improvement in the latter months [5-7].

Targeted therapies with good preliminary evidence to date include constraint induced aphasia therapy (CIAT); use of language in games to make, reject or clarify requests for targeted items for 30 hours over 2 weeks [5,8,9]. A systematic review of 10 studies conducted over the decade concluded that evidence for this technique is favourable [10]. Model oriented aphasia therapy (MOAT), which tailors treatment according to a patient’s individual symptoms, was found to be comparable to CIAT when delivered with similar intensity [11]. Raymer *et al*. found personal relevance or ‘salience’ of the language material being practiced to be important when targeting therapy [6]. While the optimum intensity remains unclear, it is generally acknowledged that for stroke rehabilitation regular, repetitive therapy practice is a factor in treatment success.

The resources required to achieve intensive therapy in the long term is prohibitive in the current financial climate and lower cost options for the support of repetitive intensive practice are needed. Non-speech and language therapy professionals have been employed successfully to support therapy activity [4,12,13].

Computer therapy, developed for the treatment of aphasia, has been reported to be useful in the provision of targeted language practice and provides opportunities for independent home practice as part of a self-management approach to maximise practice intensity, improving outcomes for reading, spelling and expressive language [13-17]. The Department of Health report, ‘*Our Health, Our Care, Our Say*’ [18], recommends self-management for long term conditions supported through technological innovation [18]. However, to date, studies of self-managed computer therapy for aphasia have been limited to descriptive case series with only three reported RCTs; two for treatment of reading disorders and one for treatment of word finding [13,14,19]. Although these studies were not fully powered, they indicate potential effectiveness of computer therapy. Such computer-based services for long term management of aphasia therapy could provide a low cost therapy option which is acceptable to patients and families. However, the actual cost effectiveness has not been definitively tested.

The StepbyStep© computerised approach to long term aphasia therapy combines current evidence underpinning language therapy with practical considerations of treatment delivery. Skills of a qualified speech and language therapist are used to select individually targeted therapy exercises, computer software is provided for regular self-managed practice of therapy exercises and volunteers or assistant SLTs support language practice and computer use [20]. A pilot study evaluating this approach was carried out with 34 people with persistent aphasia. They were randomly assigned to using computer software designed for treating aphasia, or usual long term care (most frequently this was social support). On average people with aphasia practiced their speech exercises on the computer independently for 25 hours over five months. The therapy showed statistically significant improvement in the ability to use spoken words when compared to usual care (*P* = 0.014). The results indicated that self-managed computer therapy supported by volunteers (a total of four hours on average) could help people with aphasia to continue to practise, improving their vocabulary and confidence talking [13]. Patients and carers found it an acceptable alternative to face-to-face therapy [21]. Self-managed computer therapy could therefore improve the quality of life of people with persistent aphasia at relatively low cost, and exploratory economic analysis has suggested considerable potential for the intervention to prove cost effective [13,22].

The aim of this study is to provide definitive evidence of the clinical and cost effectiveness of targeted, intensive speech and language impairment-based therapy intervention for word finding delivered through self-managed computer exercise for persisting post-stroke aphasia. This builds on the pilot RCT which explored possible effects, and informed measures, feasibility, recruitment rates, adherence, cost effectiveness analysis and a power calculation. The current study was commissioned by the United Kingdom National Institute for Health Research, having considered the limitations in the current evidence base.

### Objectives

The primary objectives of the study are:To establish whether self-managed computerised speech and language therapy for aphasia related word finding problems after stroke increases the ability to use vocabulary of personal importance (impairment).To establish whether self-managed computerised speech and language therapy for word finding problems after stroke improves functional communication ability in conversation (activity).To investigate whether patients receiving self-managed computerised speech and language therapy perceive greater changes in social participation and quality of life (participation).To establish whether self-managed computerised speech and language therapy is cost effective for persistent aphasia post stroke.To identify whether any effects of the intervention are evident 12 months after therapy has begun.

Secondary objectives include investigating the generalisation of treatment to retrieval of untreated words (impairment); the use of treated words in conversation; the carer perception of communication effectiveness (participation) and identification of any possible adverse events. Carers’ own quality of life will be measured. Fidelity to treatment will also be monitored.

## Methods/Design

### Design

The study will use a pragmatic, parallel group randomised controlled adjunct trial design. The intervention under test or attention control will be delivered in addition to usual care. Outcomes will be compared for people who are four months or more post stroke, with persistent aphasia who are randomly allocated to either: usual care, self-managed computerised speech and language therapy in addition to usual care or attention control in addition to usual care.

Each participant will be in the trial for 12 months. Participants will be identified and recruited over an 18-month period in total, and 15 months at each site. Each participant will receive their intervention for six months, with follow-up at six, nine and 12 months. The study has an internal pilot phase with criteria for progression to completion of the full RCT. There are no formal statistical criteria for stopping the trial early. Decisions to stop the trial early on grounds of safety or futility will be made by independent data management and ethics committee members. The protocol conforms to the Consolidated Standards of Reporting Trials (CONSORT) guidelines for non-pharmacological studies (Figure 1) [23].

**Figure 1 Fig1:**
[figure not shown]
**Progression of participants through the trial (CONSORT diagram).** SLT = speech and language therapist; ITT = intention to treat.

### Ethics approval

The study protocol was approved by Leeds West research ethics committee (reference number: 13/YH/0377). Additional approval was granted for Scotland by the Scotland A research ethics committee (reference number: 14/SS/0023). The University of Sheffield is the sponsor. The trial is registered with the International Standard Randomised Controlled Trials database ISRCTN (reference number: 68798818) and is commissioned by the National Institute for Health Research.

### Participants

A total of 285 participants who have a diagnosis of aphasia as a consequence of a stroke will be recruited from approximately 20 speech and language therapy departments across the United Kingdom. The study will also be advertised at voluntary groups and using posters in libraries and GP surgeries in each locality so that potential participants can self-present to the local research team.

### Inclusion criteria

Participants will be included if they meet the following criteria:Aged 18 or over;Diagnosis of stroke(s);Onset of stroke at least four months prior to randomisation;Diagnosis of aphasia, subsequent to stroke, as confirmed by a trained speech and language therapist;Ability to retrieve 10 to 90% of words on the Comprehensive Aphasia Test Naming Objects subtest (score of 5 to 43 out of 48);Ability to perform a simple matching task in StepByStep with at least 50% accuracy (to confirm sufficient vision and cognitive ability) andAbility to repeat at least 50% of words in a simple word repetition task in the StepByStep© program.

### Exclusion criteria

Participants will be excluded from the study if they meet any of the following criteria:They have another pre-morbid speech and language disorder caused by a neurological deficit other than stroke (a formal diagnosis can be reported by the participant or relatives and confirmed by the recruiting speech and language therapist).They require treatment for a language other than English (as the software is in English).They are currently using the StepbyStep© computer programme or other computer speech therapy aimed at word retrieval and/or naming.

### Procedures

#### Identification

Potential participants will be contacted by the research speech and language therapist in each project centre and provided with information on the project. They will be contacted within a fortnight to establish whether they are interested in knowing more about the study. If they are interested, the research speech and language therapist will make an appointment to visit them at home. The number of those contacted but who cannot be followed up on or who are not interested in learning more and the reason for this will be recorded.

#### Screening for eligibility

Eligibility will be established on the first visit. The speech and language therapist will request verbal consent to carry out the Naming Objects subtest of the Comprehensive Aphasia Test [24]. This test is used in routine practice and will establish the severity of the word finding deficit. If the word finding score is less than 10%, or greater than 90%, an explanation will be given that this type of computer therapy is not suitable for them. If the potential participant has eligible word finding scores, the research speech and language therapist will ask them to try a simple repetition task to confirm their repetition ability, followed by a matching task on the computer to confirm ability to see the screen and perform simple computer related actions.

#### Recruitment

The level of support required to enable a person with aphasia to provide informed consent is dependent upon the severity and profile of the aphasia. In order to provide information in a format consistent with each individual's language ability, a consent support tool (CST) will be used [25]. The research speech and language therapist at each site will request verbal consent from the potential participant to carry out part A of the CST. The result will indicate the style of information they are most likely to understand in part B. Participants will be given sufficient time to consider their participation before informed consent is taken by a research speech and language therapist. Participants providing their own informed consent will be provided with an aphasia-friendly consent form. If potential participants with severe aphasia indicate an interest, a relative (in Scotland this will be the person’s legal representative or nearest relative) will be asked to read an information sheet detailing their responsibility, and will be asked to sign a carer declaration on behalf of their relative with aphasia (in Scotland they will be asked to sign a consent form). For those participants with a carer, the carer will be asked if they are willing to complete some outcome measures related to their own quality of life and perception of their relative’s communication ability. They will be provided with the carer information sheet detailing their potential involvement and will be asked to sign a separate consent form. Informed consent will be obtained from each participant where they are able to give it, or consent or carer declaration will be obtained by the carer or legal representative where the participant is interested in participating, but is unable to provide their own fully informed consent.

### Baseline assessment

Initial assessment will be performed by the local research speech and language therapist once informed consent has been given. This will include collection of the following demographic data: aphasia type, age, gender, time post-onset of stroke and type and location of stroke (if known). Baseline information will also include results of the standardised naming test - Naming Objects subtest of the Comprehensive Aphasia Test (performed as part of eligibility testing during screening) and the Comprehension of Spoken Sentences subtest of the CAT to provide information on the comprehension ability of the participants [24]. Baseline measures relating to the study outcomes are summarised in Table 1.

**Table 1 Tab1:** **Summary of measures**

**Outcome**	**Measure**	**Method of collection**
Change in word finding ability	Naming of 100 personally relevant words	Taken at baseline by blinded SLT recruiting participant 6, 9 and 12 months by separate blinded SLT.
Change in functional communication	10-minute videoed conversations structured around topics of personal interest. Activity scale of TOMS used to measure conversational ability	Conversations at baseline by blinded SLT. Separate blinded SLT follows same topic guide at 6, 9 and 12 months. Videos randomised and rated centrally by blinded assessors.
Change in patient perception of communication and quality of life	COAST self-reported questionnaire.	Administered by blinded SLT at baseline. Separate blinded SLT at 6, 9, and 12 months.
Generalisation to untreated words	Naming Objects subtest from Comprehensive Aphasia Test	As above
QALYs for cost effectiveness	EQ-5D for patient and carer (accessible and by proxy)	As above
Carer quality of life	Carer COAST and CarerQol	Self-administered
Cost of intervention	Diaries of time spent on intervention	Self-administered by SLTs, SLTAs and volunteers
Cost of usual care	Diaries of time spent on usual care	SLT collects data from usual treating therapists and participants at baseline, 3, 6, 9 and 12 months
Carer perception of change in communication	Carer COAST	Collected by blinded SLT at baseline. Separate blinded SLT at 6, 9, and 12 months.
Negative effects of treatment	Patient diary to record any difficulties and/or negative impacts of intervention	Patients and carers - central team to send monthly letter reminding to send back in prepaid envelope.
Intervention adherence	Software tailoring checklists. Volunteer and/or assistant feedback forms. Software key files. Puzzle book and telephone support feedback.	Completed by SLT, monitored by central study team. Self-managed practice monitored by central study team. Puzzle book completion and telephone support recorded by member of central study team.

SLT = speech and language therapist; TOMS = Therapy Outcome Measures; COAST = Communication Outcomes After Stroke questionnaire; SLTA speech and language therapy assistant.

### Outcome measures

#### Primary

Change in the number of words (personally relevant to the participant) named correctly at 6 months from baseline will be measured by a naming task of 100 pictures presented on the computer.Change in functional communication will be measured by blinded ratings of video-recorded conversations between unfamiliar speech and language therapists blinded to treatment allocation and participants at six months. Conversations will be structured around topics of personal relevance to the participants by the speech and language therapist performing an assessment to ensure the sensitivity of the measure. The same topic guide will be followed by blinded speech and language therapists performing outcome measures. Independent speech and language therapists blinded to treatment allocation and measurement time point will rate the videoed conversations at the project coordinating centre using the activity scale of the Therapy Outcome Measures (TOMS) [26].

#### Key secondary

Improvement in patient perception of communication will be measured using the Communication Outcomes After Stroke (COAST) questionnaire at six months - a patient-centred, patient-reported measure of communication related activity, participation and quality of life [27].

#### Other secondary

Evidence of treatment effect will be measured by repeating all outcome measures at nine and 12 months from baseline, in addition to the primary end point of 6 months. The nine-month time point is included as an interim measure as drop out from the study was found to increase over time in the pilot study [13].

Generalisation of treatment to retrieval of untreated words will be measured using the Naming Objects subtest from the Comprehensive Aphasia Test. Carer perception of communication effectiveness will be measured using the Carer COAST questionnaire [28]. Carer quality of life will be measured using the last five items of the Carer COAST questionnaire [28] and the CarerQol questionnaire [29]. Negative effects of treatment will be reported through diaries. Table 1 summarises the main measures and methods of data collection. Follow-up assessments will be conducted within one month of the target time point.

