##### Self-managed computerised therapy intervention

A structured intervention is proposed in addition to usual care as tested in the pilot study. The intervention targets word retrieval as it is one of the challenges most frequently experienced by people with aphasia, restricting their communication. The three components of the intervention are as follows:Qualified speech and language therapist assessment, tailoring of exercises and monitoringThe speech and language therapist at each site will tailor computer exercises to the individual using 100 words of personal relevance chosen by the participant. Photographs imaging the 100 words will be selected from those existing in the software, or can be added from a digital camera or from image stores on a computer. The computer software (StepbyStep© by Steps Consulting Ltd, Gloucester, UK) [30] enables the speech and language therapist to select exercises using these words that follow steps in the therapy process that the therapist would take if delivering it face to face. The speech and language therapist bases the selection of exercises on language skills demonstrated in the initial language assessments. The speech and language therapist will provide initial demonstration of the software exercises, check that the individual is able to use the software and monitor the appropriateness of the tailored exercises. This is expected to take only three to four hours, based on the pilot study [13], as the computer intervention is predominantly self-managed by the patient.Regular self-managed practiceThe participant will then be asked to work through the exercises on the computer and be encouraged to practise each day for 20 to 30 minutes. Participants will be given a six-month period to work though the therapy material on the computer and practise using the new vocabulary in their daily lives. As this is a pragmatic trial, those participants who have the software installed on their own computers will not be prevented from continuing to practise if they wish, following the six-month supported intervention time. Any continued use of software beyond the six months will be recorded.Volunteer support to assist with treatment adherence and carry over into daily activityTo enhance treatment adherence, the speech and language therapist will provide training to local volunteers who already have a working relationship with the SLT department or SLT assistants based in the department. They will use the three-hour training programme and instruction book (University of Sheffield, Sheffield, UK) developed and evaluated during the pilot study. The volunteer will be asked to visit the participant once a month for an hour, or every two weeks for half an hour (to suit the patient), carrying out the following tasks: provide technical assistance; observe and encourage use of computer exercises; check results and discuss difficulties; assist the participant to move on to harder tasks in the therapy process pre-programmed by the speech and language therapist; encourage the use of new words in everyday situations, conversation and discussions with family about how to encourage use and encourage re-use of completed exercises over time.The participants will be able to contact the volunteer or SLTA by telephone for technical advice on computer use between planned visits if necessary. Volunteers and SLTAs will be asked to complete a feedback form on each face-to-face session with a participant and send it to the therapist to enable them to provide tailored advice and support. They therapists are also encouraged to meet with all the volunteers/SLTAs together every two months for support and discussion of issues arising.The majority of the practice time involved in the intervention is self-managed by the participant through regular use of the aphasia computer software. The therapists, SLTAs and volunteers will be asked to keep diaries of resource use showing direct and indirect (telephone and computer set up) time spent and therapist grade (see Table 1).

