The therapy under investigation is a complex intervention of word finding therapy for aphasia. Previous studies, including the pilot study informing this protocol, have shown that people with aphasia learn the words that are meaningful to them more successfully than those they have little functional need for. As in many rehabilitation interventions, this therapy is driven by the patient’s own goals. Communication needs to achieve different goals are discussed with the therapist and a range of words key to achieving those goals are identified. The personalisation of the therapy goals requires some personalisation in the measurement of whether they have been achieved. The design of outcome measures which can be used to make group comparisons whilst maintaining accurate measurement of individual goals was a challenge. Discussions resulted in two primary outcome measures. The first measures word finding ability whereby all participants have comparable word finding scores from naming 100 pictures. Measurement of word finding of personally meaningful and useful words is achieved by allowing the 100 words to be different for each individual according to their goals. Similarly, the second measures ability to communicate in conversation. All conversations are rated using the activity scale of the TOMS so group comparisons can be made. Measurement of individual goals is maintained by structuring the conversations around the communication areas identified as personally relevant by each individual.

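### The score used for generalisation to untreated words can include words the participant has practised, because nothing in the article separates the two sets

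*Protocol article*

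**What the plan says.** The Objectives section of the protocol article lists generalisation to untreated words as a secondary objective at the impairment level. The measure is given under Other secondary: "Generalisation of treatment to retrieval of untreated words will be measured using the Naming Objects subtest from the Comprehensive Aphasia Test". Table 1 repeats it as "Naming Objects subtest from Comprehensive Aphasia Test", with no item exclusion. All outcomes are repeated at six, nine and 12 months.

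The practised words are described under Self-managed computerised therapy intervention, where the therapist is to "tailor computer exercises to the individual using 100 words of personal relevance chosen by the participant". On the pictures, the same section says: "Photographs imaging the 100 words will be selected from those existing in the software, or can be added from a digital camera". The Discussion explains that personal relevance is achieved by "allowing the 100 words to be different for each individual according to their goals".

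The same subtest serves two other purposes: eligibility (a score of 5 to 43 out of 48) and the severity strata for randomisation. It is given at screening. Table 1 has each participant name their own 100 words at baseline, and randomisation follows the baseline assessment.

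**The concern.** A test of generalisation is informative only if its items were not trained. Here the test is a fixed standard set of objects, while the trained set varies by person and is drawn from words useful in daily life. Nothing in the article prevents the two sets from sharing items. Where they do, the software practice on the shared object is given in one arm only, so randomisation does not balance its effect.

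What is at stake is the meaning of this secondary result. A positive difference on the full subtest could reflect wider recovery of word finding, direct practice of some test items, or both, and the score as planned cannot tell these apart. Separating treated from untreated words is the purpose of the outcome.

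**Working it through.** The plan gives no figure for this point, so there is none to reproduce. The check compares the text and then sizes the effect under a stated assumption.

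**Text check**

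- Measure: the full Naming Objects subtest (Other secondary; Table 1).
- Trained set: 100 words per participant, individually chosen, with pictures from the software or added (intervention section; Discussion).
- Rule separating the two: none in the outcome sections, the intervention section, Table 1 or the Statistical analysis section.
- Order of events: the subtest is taken at screening and the 100 words are named at baseline, before randomisation. Nothing in this order stops a subtest object from being listed. It does mean that a list exists in all three arms before allocation.

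**Size**

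Inputs:

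- d = 10 percentage points, the planned effect on practised words (Assumptions for the sample size calculation).
- Maximum subtest score 48 (Inclusion criteria).
- f = share of subtest objects on the participant's own list. The article does not give it; 5 to 25% is assumed here.
- g = true generalisation to unpractised objects, in percentage points.

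Expected between-arm difference on the full subtest = f × d + (1 − f) × g.

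Error as a measure of g = f × d + (1 − f) × g − g = f × (d − g).

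The error favours the intervention whenever practised words gain more than unpractised ones (d > g), and it is largest in the case g = 0, where it equals f × 10:

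| Overlap f (assumed) | Spurious gain, points in 100 | On the 48-point scale |
|---|---|---|
| 5% | 0.05 × 10 = 0.5 | 48 × 0.005 = 0.24 |
| 10% | 0.10 × 10 = 1.0 | 48 × 0.010 = 0.48 |
| 25% | 0.25 × 10 = 2.5 | 48 × 0.025 = 1.2 |

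For scale, the word-finding SD in the sample size section is 17.38 points. At 10% overlap the spurious gain is 1.0 / 17.38 = 0.06 SD, and at 25% it is 2.5 / 17.38 = 0.14 SD. That SD belongs to the practised-word outcome, so this is only a rough yardstick for the subtest.

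If only off-list objects are scored, f = 0 and the error is f × (d − g) = 0.

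**The case against.** The strongest reply is that this point rests on the silence of a condensed article. Nothing in it shows that a subtest object ever becomes a practised word. The full protocol or the analysis plan, neither shown, may hold an exclusion or scoring rule. The Discussion also describes word choice as driven by goals discussed with the therapist, which may make overlap with a standard object set uncommon. And the outcome sits outside the formal testing sequence, so no declared significance depends on it. All of this limits the size and certainty of the point. It does not remove it, because the article goes further than silence: it names the whole subtest as the measure of untreated words while leaving the trained set to individual choice.

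A reader might infer that the error must always favour the intervention because only that arm trains the words. The article does not support this. Usual care, which continues in every arm, may include face-to-face therapy for language impairment, so listed words may be practised anywhere. Only the software practice is specific to the intervention arm. The direction is likely, not certain.

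A reader might also add that the separate objective on "the use of treated words in conversation" will have no data. That is too strong. The outcome sections name no score for it, and the Therapy Outcome Measures (TOMS) activity scale is applied to the videos as a rating of conversational ability. But the conversations are recorded at every assessment, and a named score for a minor secondary objective may stand in the full protocol. This deserves a note and does not carry the point.

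**Conclusion.** The point holds as a minor, correctable weakness in how one secondary outcome is scored. As written, the generalisation score can count directly practised objects as untreated. Any overlap would tend to inflate apparent generalisation, by about 0.5 to 2.5 points in 100 at an assumed overlap of 5 to 25%.

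That range rests on three assumptions: the overlap share, which the article does not give and which may be near zero; a gain on overlapping objects equal to the planned 10 points; and no true generalisation. With some true generalisation below 10 points, the inflation is smaller.

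The article does not support the stronger conclusion that the generalisation result will be wrong or that the objective goes unanswered. It shows that contamination is possible, not that it occurs. The primary outcomes and the key secondary outcome are unaffected.

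**What to change.** Add a scoring rule for the generalisation outcome:

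- Using each participant's word list as fixed before randomisation, identify the subtest objects that are not on it.
- Analyse the percentage correct on those objects, with the same object set at baseline and at each follow-up.
- Base the generalisation conclusion on this off-list score and report the full standardised score beside it.
- Keep the full score for eligibility and stratification.

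Because every arm has a list before allocation, the exclusion does not depend on arm. It needs no new assessment and leaves the intervention unchanged. The cost is fewer items for some participants and a denominator that varies between them, so the off-list score is not the standardised test score. Reporting the overlap share by arm would show whether the issue mattered.

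A minor note on treated words in conversation: if the full protocol has no score for this objective, either count listed words from the existing videos or withdraw the objective. Any count should be made separately from, and after, the blinded TOMS rating, since a rater holding the word list could be influenced when scoring a primary outcome. The work is not trivial. With no dropout, 285 participants × 4 assessments = 1,140 recordings, and at ten minutes each that is 11,400 minutes, or 190 hours of viewing.
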